### Computation of Sample Size

The study aims to assess the relative efficacy of an EMDR intervention protocol for patients with FEP versus TAU mainly in terms of stabilization and clinical improvement, reduction of anxious, depressive, somatic and/or psychotic symptoms, among others. For this reason, the main variable used is the number of clinical relapses after the intervention, with a follow-up of up to 12 months. Using previous studies as a basis (33), the sample size has been calculated based on a survival analysis with the statistical package “powerSurvEpi” for R, (http://www.r-project.org/) using an alpha = 0.005 instead of 0.05 to allow correction for multiple comparisons. The number of patients required to detect a hazard ratio = 2 in a Cox regression with a statistical power of 80% and alpha = 0.005 is n = 36 per intervention group (two groups, total n = 72). According to Chambless and Hollon (29), a sample of this size should show clinically relevant differences. Assuming a loss percentage of approximately 10–15% of the patients in the study, it would be necessary to recruit approximately 80 patients, 40 for each branch of intervention.

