### Dropouts and Follow-Up

Any patient who is admitted to hospital following a clinical relapse during the 5-month intervention period will be considered to be dropout and will be excluded from the trial. In the case of relapse during follow-up, patients will be removed from the study and relapse-related factors will be collected for subsequent analysis.

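### The target of 80 preserves the required 72 patients only at the lower end of the stated 10–15% loss, and it is unclear whether patients excluded after a relapse admission count towards that loss

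*Protocol article*

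**What the plan says.** Computation of Sample Size sets the requirement at "n = 36 per intervention group (two groups, total n = 72", as the number needed to "detect a hazard ratio = 2 in a Cox regression with a statistical power of 80% and alpha = 0.005". It then inflates for losses: "Assuming a loss percentage of approximately 10–15% of the patients in the study, it would be necessary to recruit approximately 80 patients", split 40 to each arm. The Abstract and Participants give 80 without qualification. The same section describes the primary variable thus: "the main variable used is the number of clinical relapses after the intervention, with a follow-up of up to 12 months".

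Dropouts and Follow-Up says that a patient admitted to hospital after a clinical relapse in the 5-month intervention period "will be considered to be dropout and will be excluded from the trial". Patients who relapse later, during follow-up, are removed from the study, but their relapse-related data are collected.

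Statistical Analysis specifies intention-to-treat (ITT) for the main analysis, with last observation carried forward (LOCF) for losses. Hypothesis 1 compares relapses at T1 (6 months) and at T2 (12 months).

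**The concern.** A loss allowance given as a range tells the reader that the recruitment figure holds across that range. Here it holds only at the most favourable end, so the trial would miss its own required number at most of the losses it says it expects.

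The dropout rule adds a second uncertainty. Patients admitted for relapse during the intervention are dropouts by the protocol's own definition, yet the sample-size paragraph does not say whether they are part of the 10–15%.

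The rule matters beyond headcount. Relapse is the primary outcome, and the excluded patients have had that kind of event after randomisation. Excluding them is hard to square with ITT. It also takes events away from an analysis whose power depends on events.

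**Working it through.** **Inputs from the protocol.** Required N = 72 (36 per arm); loss d = approximately 10–15%; recruited approximately 80 (40 per arm); hazard ratio 2; power 80%; alpha 0.005, sidedness not stated. No relapse or event probability is given.

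**1. Reproducing the stated figure.** Recruits needed = N/(1 − d). At d = 10%: 72/0.90 = 80.0. The stated 80 is reproduced exactly. The cruder N × (1 + d) gives 72 × 1.10 = 79.2, which also rounds up to 80.

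**2. The rest of the range.**

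| Loss | 72/(1 − d) | Recruits needed | With equal arms | Left from 80 |
|---|---|---|---|---|
| 10% | 80.0 | 80 | 80 | 72 |
| 12.5% | 82.3 | 83 | 84 | 70 |
| 15% | 84.7 | 85 | 86 | 68 |

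The cruder formula does not reach 80 at 15% either: 72 × 1.15 = 82.8, so 83. The largest loss that 80 absorbs while keeping 72 is 1 − 72/80 = 10.0%.

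**3. Margin for relapse exclusions.** At a 10% loss the margin is 80 × 0.90 − 72 = 0, so any exclusion beyond the 10% takes the trial below 72, whatever the relapse rate. If the 10–15% already includes relapse admissions, the range left is simply 72 to 68. If they come on top, the result depends on a rate r that the protocol does not give. As an illustration only, 80 × (1 − r) × (1 − d) for an assumed r of 5–20% gives 68.4 to 57.6 at d = 10% and 64.6 to 54.4 at d = 15%.

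**4. The dropout rule beside the other sections.**
- Statistical Analysis: ITT, which keeps randomised patients in the analysis. Dropouts and Follow-Up: certain randomised patients are excluded because of what happened after randomisation.
- Hypothesis 1: relapses compared at T1, the 6-month visit. The intervention fills the first 5 of those months, and this is the period in which relapses leading to admission cause exclusion.
- Computation of Sample Size: relapses are counted once the intervention is over. This fits the exclusion better, but it does not fit a T1 comparison of relapse or ITT from randomisation.

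**5. Why headcount cannot be turned into power here.** Events needed for hazard ratio 2 and 80% power at two-sided alpha 0.005:
- Schoenfeld: 4 × (2.807 + 0.842)² / (ln 2)² = 111.
- Freedman: 9 × (2.807 + 0.842)² = 120.
- One-sided, the figures are 98 and 106.

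All exceed 72 patients. Even if every one of 72 patients had an event, two-sided power would be 51% (Freedman) to 55% (Schoenfeld). The nominal 80% is therefore not a valid starting point for working out the power lost in going from 72 to 68.

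**The case against.** The strongest defence is that both figures are hedged as approximate, that 80 is the exact answer at one end of the stated range, and that the gap at the other end is only 5 patients. This stands in part: 80 is not an arithmetical error, and the shortfall is modest. It does not rescue the sentence, because 80 is fixed elsewhere as the sample size and any loss above 10% leaves fewer than 72.

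A reader might infer that relapse dropouts were left out of the allowance. The protocol does not support that. It gives one undivided loss percentage, which may already contain them, and adding them on top could count them twice. The exclusion also applies only to relapses that lead to admission, so removing every expected relapse would overstate it. What can be said is that the allowance is not shown to include them.

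A reader might also scale the nominal 80% power by the surviving headcount. That is unsupported on two counts: the 80% at 72 patients does not follow from the stated inputs, and Cox power depends on events rather than patients.

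Finally, under ITT a patient lost early still contributes censored time, so a loss is not simply one patient subtracted. That is fair, but the protocol itself inflates by headcount, and its statement should hold on those terms. It could also be argued that exclusion means only the end of participation, with the data retained. The text does not say so; it mentions data collection only for relapses during follow-up.

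**Conclusion.** The point holds in limited form. The recruitment figure matches the stated loss range only at 10%. At 15% the requirement is 85 (86 with equal arms), and 80 leaves 68, which is 4 short of 72. This rests only on the protocol's own numbers.

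Whether relapse exclusions widen the gap cannot be determined, since neither their rate nor their place in the 10–15% is stated. At a 10% loss there is no room for them. Separately from the count, the exclusion rule conflicts with the ITT statement and removes patients who have had the type of event the trial counts.

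No power figure should be attached to the shortfall. The base of 72 does not give 80% power for a hazard ratio of 2 at alpha 0.005. That is a larger fault, and raising 80 to 85 would not repair it.

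**What to change.** 1. In Computation of Sample Size, state that 80 patients allow for a 10% loss and that 68 would remain at 15%. State whether the loss percentage includes patients excluded after a relapse admission. This point calls for no extra enrolment.
2. Reconcile Dropouts and Follow-Up with Hypotheses, Computation of Sample Size and Statistical Analysis. Randomised patients who relapse during the intervention should stay in the ITT primary analysis with the relapse counted as an event, and the post-intervention wording of the endpoint should be aligned to match. This concerns analysis only. Whether such patients continue the study therapy is a clinical matter on which no view is taken here.
3. Do not add a power figure for 68 patients derived from the nominal 80%. Recompute any power statement from expected events, together with correction of the base of 72.

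The cost is a less favourable stated loss tolerance and small edits to the endpoint and dropout wording. Keeping the enrolment target unchanged here does not mean that 80 patients are enough for the stated power.

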### Statistical Analysis

The distribution of socio-demographic, clinical (including psychological trauma), functionality, quality of life and treatment adherence characteristics among baseline groups will be analyzed using descriptive statistics. Continuous variables with a normal distribution will be analyzed with the Multivariate Variance Analysis. The change of the clinical variables of functionality and quality of life with respect to the baseline assessment at strategic points of the intervention will be analyzed by ANOVA with repeated measurements, including time factors, treatment conditions and their interaction. For those cases in which the premises of normality are not fulfilled, the Wilcoxon test will be used. The differences between groups, for the categorical and main clinical variables, will be analyzed by means of the Chi-square test. Those variables that are statistically significant can be used as covariates for a logistic or linear regression study of the factors associated to the magnitude of the effect and determine which variables are the best predictors of functioning. The effect size index (Hedges g or r de Pearson index) will be estimated in case of correlation indexes of each of the analyses performed. The statistical software used for the analyses will be the latest available version of the SPSS (v. 23).

For the main statistical analysis, we will conduct an intention-to-treat (ITT) analysis. We will impute lost to follow-up with the Last Observation Carried Forward (LOCF) method.

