## Methods

### Design and Study Setting

This multicenter phase II rater-blinded randomized controlled trial will involve the participation of four different centers in Catalonia: Hospital Parc de Salut Mar, Vic Hospital Consortium, University Hospital Mutua of Terrassa and Althaia Xarxa Assistencial Universitària of Manresa. The Hospital Parc de Salut Mar is a center of reference for mental health treatment and research, among other disciplines, and the collaboration with the rest of the institutions will ensure the recruitment of the complete sample.

Participants will be randomized to either treatment as usual (TAU) or to 20 individual 60-minute EMDR sessions over 5 months, as well as TAU. EMDR therapists participating in this trial are highly experienced, have received advanced training in EMDR protocols, and were recruited through face-to-face interviews. Assessments will be carried out at three time points: baseline (T0), post-treatment at 6 months (T1) and at 12-month follow-up (T2) (see **Table 1**). The clinical raters carrying out evaluations will be blind to the participants’ research condition; however this is not a double-blind study as it is not possible to mask from the patient whether they are undergoing EMDR therapy or not due to its use of bilateral stimulation.

**Table 1 T1:** SPIRIT Flow diagram: Schedule of enrolment, interventions and assessments.

Timepoint**	Study Period			
	Enrolment	Allocation	Post-allocation	Close-out
*-t_1_ & t_0_*	0	*T_1_*	*T_2_*

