### Study Aim

The main outcome of this project is to analyze whether EMDR therapy, as an adjuvant to TAU, is effective in reducing relapses in patients with an affective or non-affective FEP and a history of comorbid psychological trauma associated with first hospital admission and/or previous stressful life events. A range of scales, highlighted below, will be used to determine changes in psychiatric symptoms (see *Instruments and Measures*).

The secondary outcome includes whether EMDR therapy, as an adjuvant to TAU, is effective in reducing psychiatric symptoms and post-traumatic stress symptoms, in improving the overall functionality and quality of life associated with health, as well as adherence to pharmacological treatment. A range of clinical scales will be used the evaluate changes from baseline (see *Instruments and Measures*).

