### Hypotheses

1. Patients in the EMDR group will show fewer relapses compared to the control group after therapy (T1) and at the 12-month follow-up visit (T2).2. Patients in the EMDR group will show fewer psychiatric and trauma-related symptoms compared to the control group after therapy (T1) and at the 12-months follow-up visit (T2).3. Patients in the EMDR group will improve their functional capacity in comparison to the control group at evaluations after therapy (T1) and at the 12-months follow-up visit (T2).4. Patients in the EMDR group will show a better adherence to pharmacological treatment in relation to the control group after therapy (T1) and at the 12-month follow-up visit (T2).

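### Functioning and quality of life are analysed with baseline as a level of the time factor instead of as a covariate, and the Wilcoxon fallback is not defined

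*Protocol article*

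**What the plan says.** All points are in the protocol article. Under Statistical Analysis, the outcome is "The change of the clinical variables of functionality and quality of life with respect to the baseline assessment at strategic points of the intervention", and it "will be analyzed by ANOVA with repeated measurements, including time factors, treatment conditions and their interaction". By Tables 3 and 4 these variables are the GAF and the EQ-5D. The visits are "baseline (T0), post-treatment at 6 months (T1) and at 12-month follow-up (T2". Under Randomization Procedure, allocation follows the T0 assessment.

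For other continuous measures the same section says only: "Continuous variables with a normal distribution will be analyzed with the Multivariate Variance Analysis". The fallback is: "For those cases in which the premises of normality are not fulfilled, the Wilcoxon test will be used". Covariates appear once: "Those variables that are statistically significant can be used as covariates for a logistic or linear regression study". That regression looks for predictors of functioning; it is not a prespecified adjustment of the treatment comparison.

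The Study Aim section frames the secondary outcomes as change: "A range of clinical scales will be used the evaluate changes from baseline". The Hypotheses section asks for EMDR against control at T1 and again at T2. Hypothesis 3 does so for functioning, and hypothesis 2 for symptoms: "Patients in the EMDR group will show fewer psychiatric and trauma-related symptoms compared to the control group after therapy (T1".

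**The concern.** T0 precedes randomisation, so no treatment effect can exist there. Using it as an outcome level has three consequences.

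- The treatment main effect averages in a visit without an effect and is diluted.
- The interaction, which does carry the effect, is one global 2-df test. A significant result does not say whether the arms differ at T1, at T2 or at both.
- The baseline score is used less efficiently than it would be as a covariate.

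The fallback raises a different problem. A signed-rank test describes change within an arm. A rank-sum test at one visit compares arms but ignores baseline. A rank-sum test on change compares arms on change. The protocol does not say which is meant, so a normality check on the trial data could decide which question a scale answers.

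At stake are precision and interpretability for secondary outcomes in a trial sized on relapse alone.

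**Working it through.** The protocol gives no power figure for any scale, so there is none to reproduce. The only input from the document is n = 36 per arm (Computation of Sample Size, derived for relapse). **Assumed, not in the document:** outcome SD 1, effect d = 0.5 at both T1 and T2, equal correlation ρ between visits (compound symmetry), two-sided alpha 0.05.

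Power comes from the noncentral F distribution with noncentrality λ.

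**Joint 2-df test**
- Planned interaction: the arm differences are (0, 0.5, 0.5), and their squared deviations from the mean sum to (2/3)d² = 1/6. So λ = (n/2)(1/6)/(1−ρ), with F(2,140). At ρ = 0.5: 18 × 0.1667/0.5 = 6.0.
- Baseline-adjusted: given T0, each follow-up has variance 1−ρ² and their covariance is ρ−ρ². So λ = (n/2)·2d²/[(1−ρ)(1+2ρ)], with F(2,68). At ρ = 0.5: 18 × 0.5/1.0 = 9.0.

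**T2 alone (1 df)**
- Planned contrast, change from T0: variance 2(1−ρ), so λ = (n/2)d²/[2(1−ρ)], with F(1,70). At ρ = 0.5: 18 × 0.25/1.0 = 4.5.
- Baseline-adjusted: variance 1−ρ², so λ = (n/2)d²/(1−ρ²), with F(1,69). At ρ = 0.5: 4.5/0.75 = 6.0.

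| ρ | Joint λ, planned / adjusted | Joint power, planned / adjusted | T2 λ, planned / adjusted | T2 power, planned / adjusted |
|---|---|---|---|---|
| 0.3 | 4.29 / 8.04 | 43% / 70% | 3.21 / 4.95 | 42% / 59% |
| 0.5 | 6.00 / 9.00 | 57% / 75% | 4.50 / 6.00 | 55% / 68% |
| 0.7 | 10.00 / 12.50 | 81% / 88% | 7.50 / 8.82 | 77% / 83% |
| 0.8 | 15.00 / 17.31 | 94% / 96% | 11.25 / 12.50 | 91% / 94% |

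For the mean of T1 and T2 (1 df) at ρ = 0.5, the planned contrast against T0 has variance 1.5(1−ρ) = 0.75, so λ = 4.5/0.75 = 6.0 and power 68%. The adjusted comparison has variance (1−ρ)(1+2ρ)/2 = 0.5, so λ = 9.0 and power 84%.

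The direction does not depend on the assumed correlation. The ratio of planned to adjusted λ is (1+2ρ)/3 for the joint test and (1+ρ)/2 for T2 alone. Both are below 1 whenever ρ < 1, and both approach 1 as ρ does.

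**Check by simulation** (8,000 trials per setting, ρ = 0.3, 0.5, 0.7). The interaction had 44%, 57% and 80% power, the treatment main effect 48%, 40% and 34%, and the adjusted T2 comparison 59%, 67% and 83%. With no effect (4,000 trials per setting), the interaction rejected in 4.5% to 5.2% of trials, so it holds its level.

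**Wilcoxon.** No arithmetic applies. The fallback sentence names neither the form of the test nor the variable. Of the three readings above, only rank-sum on change keeps a between-arm test of change.

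**The case against.** The strongest defence is that the planned ANOVA is a legitimate analysis. Its interaction compares the arms on change, holds its type I error, and fits the stated aim of evaluating change from baseline. That stands. A reader might infer that the plan loses the between-arm test, but for the ANOVA this is not so.

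A second objection is to the size of the gain. Setting the interaction's 57% against the 84% for the adjusted mean of T1 and T2 (ρ = 0.5) would compare a 2-df with a 1-df test, under an assumed equal effect that favours the average. That stands too: like for like the gap at ρ = 0.5 is 18 points for the joint test, 16 for the mean and 13 for T2 alone, and it is only 2 to 3 points at ρ = 0.8 for the joint and T2 tests.

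Third, the ANOVA sentence clearly names only functionality and quality of life. A reader might extend the power loss to every secondary scale, but the document does not establish which method the symptom and trauma scales or the DAI-10 would receive.

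Fourth, the Wilcoxon test may be meant as rank-sum on change, and a condensed article may leave that to a fuller document. This limits the point to an ambiguity; loss of the between-arm test is a possibility, not a fact. Nor does the document give data on how skewed any scale is.

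A reader might add that repeated-measures ANOVA drops patients with a missing visit. The section specifies last observation carried forward for losses to follow-up; the merits of that are a separate issue.

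What remains is that the plan fixes a model without baseline adjustment although the score is collected. Allocation balances only group size, age, sex and years of education, so baseline scores are left to chance.

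**Conclusion.** The point holds as one of efficiency and definition, not of validity. For GAF and EQ-5D the planned analysis is valid but less powerful than a baseline-adjusted one, and its global interaction test does not itself supply the T1 and T2 contrasts. Over correlations of 0.3 to 0.8 the shortfall runs from 27 points down to 2 for the joint test, and from 17 down to 3 for T2 alone. These sizes rest on the assumed effect of 0.5, compound symmetry, 36 per arm and alpha 0.05; the direction holds for any correlation below 1 under that structure. The Wilcoxon fallback is underspecified, and under two of its three readings it would either give no between-arm test of change or ignore baseline.

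**What to change.** For GAF and EQ-5D, and for the other continuous scales measured at T0, T1 and T2 where a linear model is intended, state one mixed model with T1 and T2 as outcomes and with arm, visit, arm-by-visit, baseline score and baseline-by-visit as terms. Report the adjusted between-arm difference with its 95% CI at T1 and at T2. For non-normal scales, keep the same model with a transformation or a bootstrap confidence interval, and delete the normality-triggered switch to a Wilcoxon test.

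The cost is analysis wording only. The baseline scores are already in the schedule and no new data are needed.

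### The trial is sized on a Cox hazard ratio for relapse, but the analysis section names no survival analysis, tests the main variables by chi-square and fills in loss by LOCF

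*Protocol article*

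**What the plan says.** **Computation of Sample Size.** The endpoint is defined thus: "the main variable used is the number of clinical relapses after the intervention, with a follow-up of up to 12 months". The method follows: "the sample size has been calculated based on a survival analysis". The target is to "detect a hazard ratio = 2 in a Cox regression with a statistical power of 80% and alpha = 0.005", and the result is "n = 36 per intervention group (two groups, total n = 72" patients, raised to about 80 for 10–15% loss.

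**Statistical Analysis.** The methods listed are descriptive statistics, multivariate analysis of variance, repeated-measures ANOVA, the Wilcoxon test, chi-square, and logistic or linear regression for predictors. On group comparisons it says: "The differences between groups, for the categorical and main clinical variables, will be analyzed by means of the Chi-square test". The main analysis is intention-to-treat, with LOCF for patients lost to follow-up. There is no Cox model, log-rank test, Kaplan-Meier estimate, time-to-relapse variable or censoring rule here or elsewhere in the article.

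**Design and Study Setting.** Sessions run over 5 months and assessments are at "baseline (T0), post-treatment at 6 months (T1) and at 12-month follow-up (T2". Tables 2–4 label both T1 (6 months) and T2 (12 months) as post-treatment.

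**Dropouts and Follow-Up.** A patient admitted for relapse during the 5-month intervention period counts as a dropout and is excluded. A patient who relapses in follow-up is removed from the study, with relapse-related factors collected.

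**The concern.** A Cox analysis uses the time of each relapse and lets a patient who leaves early contribute only the time observed. A chi-square test on relapse status uses neither, so every patient needs a yes or no at the end. LOCF supplies one: a patient who leaves without having relapsed is carried forward as not relapsed. The arm that loses more patients then appears to relapse less.

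This concerns the primary outcome. Patients know whether they receive a course of up to 20 sessions, so unequal loss is plausible, and the direction of the resulting bias cannot be predicted. Nor would the reported result be a hazard ratio, the quantity on which the sample size rests.

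**Working it through.** **1. The two sections side by side**

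| Item | Computation of Sample Size | Statistical Analysis |
|---|---|---|
| Relapse measure | Relapses, sized as a time to event | Relapse not named; categorical and main clinical variables |
| Effect measure | Hazard ratio | None stated for relapse |
| Test | Cox regression | Chi-square |
| Early loss | Numbers inflated for 10–15% loss | LOCF |

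**2. The plan's own figure.** Events needed for hazard ratio 2, 1:1 allocation, 80% power, two-sided alpha 0.005 (sidedness is not stated; two-sided assumed):

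- Schoenfeld: 4(2.807 + 0.842)² / (ln 2)² = 4 × 13.31 / 0.4805 ≈ 111.
- Freedman: (2.807 + 0.842)² × [(2 + 1)/(2 − 1)]² = 13.31 × 9 ≈ 120.

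The stated 72 patients are not reproduced, because either count exceeds 72 patients even if all relapse. That is a separate point. It is noted here because restoring the Cox analysis will not repair it.

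**3. What LOCF does to the observed proportions.** Assumptions, none given in the article: 50% TAU relapse risk at 12 months, exponential relapse and loss independent of each other, 40 per arm. With relapse hazard λ and loss hazard δ per year, the proportion recorded as relapsed is

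λ/(λ + δ) × [1 − exp(−(λ + δ))].

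No true effect (λ = 0.693 in both arms):

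- TAU, 10% loss (δ = 0.105): 0.693/0.799 × (1 − 0.5 × 0.9) = 0.868 × 0.55 = 47.7%.
- EMDR, 30% loss (δ = 0.357): 0.693/1.050 × (1 − 0.5 × 0.7) = 0.660 × 0.65 = 42.9%.

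The truth is 50% in both arms. The gap of 4.8 points comes entirely from the imputation.

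Hazard ratio 0.5 (true risks 50% and 1 − √0.5 = 29.3%, a difference of 20.7 points), loss 30% TAU and 10% EMDR:

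- TAU: 42.9%, as above with 30% loss.
- EMDR (λ = 0.347, δ = 0.105): 0.347/0.452 × (1 − 0.707 × 0.9) = 0.767 × 0.364 = 27.9%.

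The recorded difference shrinks to 15.0 points.

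**4. Rejection rates.** Simulation under the same assumptions, two-sided alpha 0.05, 4,000 to 6,000 trials per scenario. Chi-square sets lost patients to no relapse; log-rank censors them.

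| True hazard ratio | Loss TAU / EMDR | Chi-square with LOCF | Log-rank |
|---|---|---|---|
| 1 | 10% / 30% | 7.8% | 5.2% |
| 0.5 | 30% / 10% | 28% | 44% |
| 0.5 | 10% / 30% | 58% | 45% |
| 0.5 | 15% / 15% | 44% | 45% |

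Repeat runs agree within about 1 percentage point. At alpha 0.005 with equal 15% loss the figures are about 15.5% and 16.8%. With no loss and no effect, the uncorrected chi-square already rejects about 6.0%, so not all of the 7.8% is due to LOCF.

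**The case against.** **The quoted sentence may not concern relapse.** The Statistical Analysis section never names relapse. The sentence stands near text on baseline characteristics and is followed by one on choosing covariates, so it could describe covariate screening. That is fair: applying chi-square to relapse is an inference, supported by relapse being called the main variable. On the other reading, though, relapse has no stated test in that section, and the LOCF rule for the main analysis still conflicts with censoring. This is therefore a conflict in the text, not detail left to an unseen analysis plan.

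**The size depends on chosen loss rates.** This stands. The 30% loss is assumed and is twice the protocol's upper figure. The direction of loss is also switched between scenarios: where EMDR loses more, chi-square rejects more often, not less. With equal loss near the protocol's rate, the choice of test hardly matters.

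**Stronger readings that the article does not support:**

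- A reader might infer that TAU patients have no date from which to start a post-intervention clock. The dropout rule applies the 5-month intervention period to any patient, and T1 is at 6 months for all.
- A reader might infer that follow-up runs to about month 17. That is one reading of an ambiguous window; month 12 from baseline fits Tables 2–4 equally well.
- A reader might see the count of relapses as a further, competing analysis. With removal at relapse, a patient can normally contribute only one, so the count is in effect the event indicator.
- A reader might infer that the test could be chosen after the data are seen. An analysis plan may exist that settles this.

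**Conclusion.** The concern holds as a mismatch between sizing and stated analysis, and this part rests on no assumed rate: the trial is sized on a hazard ratio that none of the listed methods estimates, and LOCF contradicts the censoring that a Cox model uses. It should be corrected because it affects the primary outcome.

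The numerical harm is conditional. It arises from loss that differs by arm and can go either way: false-positive rate about 7.8% against 5.2%, power about 28% against 44%, or rejection inflated to about 58% against 45%. These rest on an assumed 50% TAU relapse risk, 10% and 30% loss, exponential times and alpha 0.05. With 15% loss in both arms it is negligible. The documents do not support a claim that chi-square by itself costs much power.

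Two linked passages need attention. Excluding patients admitted for relapse during the intervention conflicts with the intention-to-treat statement, and the relapse window is ambiguous.

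**What to change.** 1. In Statistical Analysis, state one primary analysis: time to first relapse in all randomised patients, Cox hazard ratio with 95% confidence interval and log-rank test, at the alpha of 0.005 used for sizing, censored at last contact or at one fixed horizon.
2. State that LOCF does not apply to relapse, and keep chi-square as supportive only.
3. State one time origin and one horizon common to both arms, and make Design and Study Setting, Computation of Sample Size and Tables 2–4 agree on them. If the clock starts at randomisation, acknowledge that this broadens the outcome beyond relapses after the intervention.
4. Reconcile Dropouts and Follow-Up with the intention-to-treat statement, so that relapses leading to admission during the intervention count as events in the analysis.

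The cost is a few sentences of protocol change across these sections, recording of relapse and last-contact dates (which the sized Cox analysis already needs), and a slightly broader outcome definition. None of this repairs the separate shortfall in the sample size: about 111 events needed at two-sided alpha 0.005, against 72 evaluable patients.
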